**7.2. Applied Objectives**

The results of this study may contribute to the refinement of tDCS protocols in rehabilitation settings aimed at improving quadriceps muscle strength. Furthermore, the findings may provide a foundation for future research into this therapeutic modality.

**8. Research Hypotheses and Questions**

1. The effect of motor cortex tDCS on quadriceps strength in athletes following ACLR differs significantly from that of the control group.

2. The effect of motor cortex tDCS on central activation ratio, used to quantify quadriceps activation failure, differs significantly between ACLR athletes and the control group.

3. KOOS questionnaire scores differ significantly between ACLR athletes and the control group.

4. IKDC questionnaire scores differ significantly between ACLR athletes and the control group.

5. ACL-RSI questionnaire scores differ significantly between ACLR athletes and the control group.

6. What is the correlation between a-tDCS and KOOS questionnaire scores?

7. What is the correlation between a-tDCS and IKDC questionnaire scores?

8. What is the correlation between a-tDCS and ACL-RSI questionnaire scores?

9. What is the correlation between a-tDCS and VAS-reported pain scores?

**9. Definition of Terms and Concepts**

**10-20 System**

**Scientific Definition**: In electroencephalography (EEG), a cap containing multiple electrodes is placed on the human scalp to record electrical activity. The 10–20 system is a standardized method for electrode placement, consisting of 19 electrodes. Each electrode is labeled according to its anatomical location—such as temporal, parietal, frontal, or occipital regions—and its corresponding hemisphere. Even-numbered electrodes (e.g., 2, 4, 6, 8) are assigned to the right hemisphere, while odd-numbered electrodes (e.g., 1, 3, 5, 7) correspond to the left hemisphere.

The term "10–20" refers to the percentage-based spacing between electrodes relative to the total circumference of the head. Electrodes near the center of the scalp are spaced 20% apart, while those closer to the periphery are spaced 10% apart. This system is illustrated in Figure 1. Additional configurations such as the 10–10 and 20–20 systems also exist, offering finer spatial resolution by reducing the inter-electrode distance—dividing the original 20% spacing into smaller 10% intervals ([88](#_ENREF_88)).

In the present study, the 10–20 system will be used for electrode placement.

[figure not shown]

**Figure 1. The 10–20 system**

**Practical Definition:** To determine electrode placement, the 10–20 EEG system will be used. One of the key landmarks in this system is the vertex (Figure 2), located at the intersection of the line connecting the inion and nasion with the line connecting the two preauricular points. The inion is the most prominent point on the occipital bone, while the nasion is located between the forehead and the nose, at the junction of the nasal bones (Figure 3).

To identify the location of the M1, a distance equivalent to 20% of the total interaural distance is measured laterally from the vertex. This point corresponds to the C3/C4 positions in the EEG system (Figure 4) ([42](#_ENREF_42)).

[figure not shown]

[figure not shown]

**Figure 3. Location of the inion and nasion points Figure 2. Location of the Vertex**

[figure not shown]

**Figure 4. Location of the primary motor cortex (M1)**

**tDCS**

**Scientific Definition:** tDCS is a neuromodulatory technique that involves the application of a low-intensity electrical current through two electrodes—an anode and a cathode—placed directly on the scalp. This method is designed to alter neuronal excitability and cortical activity ([41](#_ENREF_41)).

**Practical Definition:** In the present study, tDCS will be applied to the M1 using anodal stimulation at an intensity of 2 mA for 20 minutes per session. The intervention will be administered over ten sessions, four times per week, with the aim of enhancing corticospinal excitability in this region.

**Pain**

**Scientific Definition :**According to the International Association for the Study of Pain, pain is defined as an unpleasant sensory and emotional experience associated with actual or potential tissue damage, or described in terms of such damage ([89](#_ENREF_89)).

**Practical Definition:** In the present study, pain will be assessed using the VAS as well as the IKDC and KOOS questionnaires.

**ACLR**

**Scientific Definition:** ACLR is a surgical procedure involving the grafting of the ACL in the knee to restore its function following injury. Common graft types include patellar tendon autografts, quadriceps tendon autografts, hamstring tendon autografts, and allografts (donor tissue from cadavers).

**Practical Definition:** In the present study, ACLR is defined as reconstruction performed using quadriceps and hamstring tendon autografts, all conducted by orthopedic specialists. Eligible participants must be 2 months post-surgery at the time of enrollment.

**Arthrogenic Muscle Inhibition**

**Scientific Definition:** Arthrogenic muscle inhibition is a reflexive inhibitory mechanism that prevents full activation of a muscle, leading to reduced dynamic joint stability and subsequent muscle atrophy ([90](#_ENREF_90)).

**Practical Definition:** In the present study, the operational definition of reflexive inhibition aligns with its scientific description and will be assessed using the superimposed burst technique (SIBT). In this method, a cutaneous electrical stimulus is applied during a maximal voluntary contraction, activating previously inactive motor units. The level of voluntary muscle activation is then quantified based on the difference between the voluntary and superimposed force outputs ([91](#_ENREF_91)).

**Central Activation Ratio (CAR)**

**Scientific Definition:** Although muscle strength is the most commonly used metric for evaluating muscular performance ([59](#_ENREF_59)), it has limitations in reflecting the optimal neuromuscular capacity of a muscle ([91](#_ENREF_91)). Therefore, the CAR is employed as a more precise indicator. CAR is defined as the ratio of maximal voluntary torque to the torque generated by superimposed electrical stimulation, and it is a widely accepted measure for quantifying neuromuscular performance of the quadriceps muscle using the Superimposed Burst Technique (SIBT). Emerging evidence suggests that this technique can reveal deficits in central activation, potentially offering unique insights into the completeness of muscle function ([92](#_ENREF_92)).

**Practical Definition:** In the present study, CAR testing will be performed using FES. Participants will execute five repetitions of maximal voluntary isometric contraction (MVIC) of the quadriceps muscle, each lasting six seconds. Once a stable torque output is observed and recorded, an electrical stimulus will be applied during the MVIC to activate motor units that were not voluntarily recruited ([93](#_ENREF_93)). The stimulation protocol will consist of a burst of ten square-wave pulses at a frequency of 100 pulses per second (pps), with a pulse duration of 0.6 milliseconds. The stimulation intensity will be set at twice the motor threshold ([51](#_ENREF_51)). Five trials will be conducted with 60-second rest intervals, and the average torque values will be used to calculate voluntary activation using Equation 1.

CAR = (MVIC torque / [MVIC torque + SIB torque]) × 100 (1)

**Maximal Voluntary Isometric Contraction (MVIC)**

**Scientific Definition:** MVIC refers to the maximum voluntary force generated by a muscle, typically quantified through torque measurements ([51](#_ENREF_51)).

**Practical Definition:** In the present study, MVIC will be assessed as the average of five isometric contraction trials of the quadriceps muscle, measured using a dynamometer.

**10. Study Methodology**

**10.1. Study Design**

This study is a randomized, double-blind clinical trial in which both the participants and the assessors are blinded to group allocation.

**10.2. Target Population and Sampling Method**

The study population consists of male athletes aged 18 to 40 years ([94](#_ENREF_94)) with a history of unilateral ACLR.

**10.3. Inclusion Criteria**

1. Athletes who are at 2 months post-ACLR surgery at the time of enrollment ([8](#_ENREF_8)).

**10.4. Exclusion Criteria**

1. History of knee surgery prior to ACLR.

2. Lower limb injury within the past 6 months, excluding the current ACLR.

3. Cardiovascular disease, history of stroke, or any condition that significantly affects motor function or physical activity capacity ([51](#_ENREF_51)).

4. History of brain surgery, brain cancer, or cranial neurological disorders ([51](#_ENREF_51)).

5. Migraine ([51](#_ENREF_51)).

6. Medical history or self-reported episodes of epilepsy or seizure disorders ([13](#_ENREF_13)).

7. Presence of intracranial metal implants ([51](#_ENREF_51)).

8. Cochlear implants or other implanted electronic devices ([51](#_ENREF_51)).

9. Balance disorders or dizziness ([51](#_ENREF_51)).

10. Active skin infections or hypersensitivity to adhesive tape ([51](#_ENREF_51)).

11. Use of sedatives or medications that alter neural activity within 48 hours prior to assessment ([13](#_ENREF_13), [95](#_ENREF_95)).

**10.5. Withdrawal Criteria**

Participants will be withdrawn from the study if they experience an increase in pain during testing procedures.

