**2. Studies Investigating Quadriceps Strength in Orthopedic Conditions Before and After tDCS**

Rodrigues et al. ([78](#_ENREF_78)) conducted a study in 2022 to evaluate the effects of a-tDCS over the motor cortex combined with open kinetic chain resistance training on muscle strength and pain perception in women with patellofemoral pain (PFP). Twenty-eight women aged 18 to 30 years with PFP were randomly assigned to two groups: a-tDCS plus resistance training, and s-tDCS plus resistance training. The intervention lasted for twelve sessions, spaced 48 to 72 hours apart.

The exercise protocol consisted of three sets of 12 repetitions of knee extension at 60% of 10-repetition maximum (10RM), with one-minute rest intervals between sets. In the a-tDCS group, a 2-mA current was applied over the motor cortex for 20 minutes prior to each resistance training session. In the sham group, stimulation was discontinued after 30 seconds. Load capacity was assessed using the 10RM test before the intervention, at session 4, session 8, and after the final session. Pain perception was evaluated using the Clarke’s sign maneuver and a VAS.

Results showed that the a-tDCS plus resistance training group demonstrated significantly greater 10RM load at session 8 (p < 0.05) and post-intervention compared to the sham group. Additionally, pain perception decreased only in the a-tDCS group following the intervention. The authors concluded that this combined intervention effectively improved quadriceps strength in women with PFP. Moreover, the reduction in pain may have contributed to the observed increase in muscle strength.

This study, using stimulation parameters similar to previous research (2 mA, 20 minutes, a-tDCS over M1), demonstrated beneficial effects on quadriceps strength in a musculoskeletal population. The concurrent reduction in pain suggests that neuromodulation via tDCS may enhance muscle performance not only through cortical excitability but also by alleviating pain-related inhibition.

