7.3. Specific Analytical Objectives

1. To compare the effect of motor cortex a-tDCS with sham tDCS on quadriceps strength in individuals post-ACLR, relative to the control group, before and after stimulation.

2. To compare quadriceps muscle strength in ACLR individuals before and after motor cortex stimulation with tDCS.

3. To compare central activation ratio to quantify quadriceps activation failure before and after motor cortex stimulation with tDCS.

4. To assess the correlation between a-tDCS parameters and total KOOS scores and domain scores in the intervention and control groups before and after tDCS.

5. To assess the correlation between a-tDCS and IKDC questionnaire scores in the intervention and control groups before and after tDCS.

6. To assess the correlation between a-tDCS and ACL-RSI questionnaire scores in the intervention and control groups before and after tDCS.

7. To assess the correlation between a-tDCS and VAS-reported pain scores in the intervention and control groups before and after tDCS.

8. To compare KOOS questionnaire scores in the intervention and control groups before and after tDCS.

9. To compare IKDC questionnaire scores in the intervention and control groups before and after tDCS.

10. To compare ACL-RSI questionnaire scores in the intervention and control groups before and after tDCS.

11. To compare VAS pain scores in the intervention and control groups before and after tDCS.

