**10.7. Study Procedures**

In this study, adult male athletes with a history of unilateral ACLR using hamstring autografts will be recruited through public announcements posted in physiotherapy clinics, outpatient centers, hospitals across Isfahan, and digital outreach via social media platforms. Participants will be selected using a non-random, convenience sampling method, based on predefined inclusion and exclusion criteria. Notably, only athletes who underwent ACLR using hamstring autografts and whose surgeries were performed using a standardized surgical technique will be eligible.

Eligible individuals will be enrolled in the study after completing an informed consent form approved by the Ethics Committee of Shahid Beheshti University of Medical Sciences. Participants will then be randomly assigned to either the intervention group or the sham stimulation group.

Prior to the start of the intervention, all participants will complete a demographic questionnaire, as well as the IKDC, ACL-RSI, and KOOS questionnaires. Pain levels will also be assessed using the VAS.

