The average torque from the five MVIC attempts will be used to quantify quadriceps strength. This procedure will be conducted prior to the tDCS intervention to establish baseline strength values. The same protocol will be repeated following completion of ten tDCS sessions to assess post-intervention changes in muscle strength.

[figure not shown]
.
[figure not shown]

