**Figure 5. Procedure for recording MVIC data and induced supra-maximal contraction in the participant**

Once each participant reaches a plateau in torque output, a supramaximal electrical stimulus will be delivered to activate motor units that were not voluntarily recruited, thereby eliciting a stronger muscle contraction. This approach is commonly used to quantify deficits in quadriceps activation following ACLR, through measurement of the Central Activation Ratio (CAR) using the Superimposed Burst Technique (SIBT) ([91](#_ENREF_91)).

For this procedure, two square-shaped electrodes (each measuring 20 cm²) will be used for electrical stimulation. One electrode will be placed proximally on the lateral aspect of the quadriceps muscle, and the other distally on the medial aspect, secured firmly with elastic bandages.

To calculate CAR, the peak voluntary torque generated immediately before the electrical stimulus is divided by the peak torque produced in response to the stimulus (i.e., the superimposed burst torque) ([51](#_ENREF_51)) (Figure 5).

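### Section 10.5 withdraws an athlete from the whole study for a pain increase during testing, where the rule could stop only that test; randomised athletes and their data can be lost needlessly (minor).

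*Protocol*

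**What the plan says.** Section 10.5 of the Protocol is a single sentence: "Participants will be withdrawn from the study if they experience an increase in pain during testing procedures". It sets no size of increase, offers no stop or repeat of the test, and makes no provision for continued treatment or data collection.

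The testing in question is described under section 10.7. Athletes two months after surgery perform unrecorded practice contractions at maximal effort, then five recorded maximal contractions; a supramaximal electrical burst is used for the central activation ratio. This is done at baseline and once more: "The same protocol will be repeated following completion of ten tDCS sessions to assess post-intervention changes in muscle strength".

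Strength is described in two places, in the same way. Section 9 has "MVIC will be assessed as the average of five isometric contraction trials of the quadriceps muscle, measured using a dynamometer", and the strength procedure has "The average torque from the five MVIC attempts will be used to quantify quadriceps strength". Neither says what to use if fewer than five are completed.

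On timing, section 10.7 places consent first, then "Participants will then be randomly assigned to either the intervention group or the sham stimulation group", and only then describes the questionnaires and VAS completed before the intervention. The baseline strength test is fixed only as preceding tDCS.

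Pain is an outcome. Item 11 of section 7.3 is "To compare VAS pain scores in the intervention and control groups before and after tDCS".

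**The concern.** The rule ends study participation when the event it responds to is a painful test. At baseline, an athlete who has already been assigned would lose the treatment and every post-treatment measurement. At the post-treatment test there is no later visit, so what can be lost is the rest of that session: the remaining contractions and any questionnaire or VAS not yet completed. The Protocol does not fix their order.

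The reason for leaving is tied to an outcome and, on the Protocol's own account, to strength. Discussing a trial in women with patellofemoral pain, the literature review says that "neuromodulation via tDCS may enhance muscle performance not only through cortical excitability but also by alleviating pain-related inhibition". If active stimulation eased pain during testing, more athletes with painful and weaker knees would leave the sham arm than the active arm, and those who remain would no longer be comparable. If it made the test more painful, the imbalance would run the other way. Even with equal loss, a small trial gives up randomised athletes.

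**Working it through.** **There is no stated figure to reproduce.** The Protocol gives no final sample size, standard deviation, effect size or dropout rate. The check is therefore a reading of the text, followed by an illustration on assumed inputs.

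**Reading, by visit**

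| | Baseline test | Post-treatment test |
|---|---|---|
| Already randomised? | Probably: section 10.7 narrates assignment first, but the order relative to the strength test is not fixed | Certainly |
| What can be lost | Treatment and all post-treatment data | Remaining trials; any questionnaires and VAS not yet done |
| Can loss differ by arm through treatment? | No, none has been given | Yes, if treatment changes pain during testing |

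**Strength value.** With a mean of five as the only description, an athlete stopped before the fifth trial has no value on that definition. A painful burst need not cost the voluntary reading, because for the activation ratio "the peak voluntary torque generated immediately before the electrical stimulus is divided by the peak torque produced in response to the stimulus": the voluntary peak comes before the burst.

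**Chance of losing someone.** With an assumed probability p that an athlete has a pain increase at testing, the chance of losing at least one of the 10 pilot participants is 1 − (1 − p)^10. For p = 5%, 10%, 20% and 30% this gives 40%, 65%, 89% and 97%.

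**Possible bias if stimulation lowers pain (all inputs assumed)**
- w = 10%, 20% or 30% of sham athletes meet the rule at an unscreened test.
- Active stimulation lowers the underlying pain score by d = 0.3, 0.5 or 0.8 SD.
- The correlation of pain with strength is ρ = −0.4 or −0.6.
- The correlation of baseline with post-treatment pain is k = 0.5 or 0.7.
- A stopped athlete has no strength value (upper case), and stimulation has no true effect on strength.

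*Rule applied at the post-test only.* The cut-off is c = z(1 − w). Mean pain among those retained is −φ(c)/Φ(c) in sham and −φ(c + d)/Φ(c + d) in active. Bias in post-test strength = ρ × (active − sham); bias in change from baseline = that × (1 − k).
- Smallest case, w = 10%, d = 0.3, ρ = −0.4: c = 1.282; sham −0.195, active −0.121; bias = −0.4 × 0.074 = −0.03 SD.
- Largest case, w = 30%, d = 0.8, ρ = −0.6: c = 0.524; sham −0.497, active −0.183; bias = −0.6 × 0.314 = −0.19 SD.
- On change: −0.030 × 0.3 = −0.01 to −0.188 × 0.5 = −0.09 SD.

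*Rule applied at both visits with the same cut-off (2,000,000 simulated athletes per k).* Post-test loss is 6% to 20% in sham and 1% to 12% in active. Bias is −0.02 to −0.14 SD on post-test strength (median over the grid −0.06) and −0.01 to −0.11 SD on change. With w of only 2% to 5%, the bias on post-test strength is −0.01 to −0.04 SD.

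*Against sampling error.* At an assumed 17 per arm (the Protocol cites an ACL-injury trial of 34 athletes in two groups), the standard error is √(2/17) = 0.343 SD. The two-visit bias is then 0.022/0.343 = 0.06 to 0.144/0.343 = 0.42 of one standard error; at the median it is about 0.06/0.343 = 0.17.

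*No effect on pain.* With d = 0 the two retained means are equal and the bias is zero.

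**The case against.** The strongest reply is that withdrawing an athlete whose knee hurts more during maximal testing two months after surgery is a safety choice for the investigator. A reader might infer that stopping the test would always be enough; no passage supports that, and the remedy must leave the decision with the clinician. The Protocol equally gives no safety reason why withdrawal should be automatic.

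A second reply is that the five-trial wording describes the routine procedure. That stands in part. A reader might infer that trials recorded before a stop are thrown away, but no section says so, and scoring an incomplete test could be settled in an analysis plan that is not shown. The withdrawal rule is different: it is a conduct rule fixed in this document, and no analysis plan can recover treatment not given or questionnaires not collected.

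Third, the baseline harm depends on an order that section 10.7 suggests but does not fix. If testing precedes assignment, a baseline withdrawal does not touch the randomised comparison. At the post-test, little of the study remains to be lost. Both points limit the size of the concern without removing it.

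Finally, the tempting inference that the rule biases the strength comparison is not supported. The evidence cited for pain relief is from women with patellofemoral pain; the one cited study after ACL reconstruction found no change in pain after a single session. Unequal loss between arms is a possibility only.

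**Conclusion.** The point holds in a limited form and is minor. As written, section 10.5 removes randomised athletes from the study, together with treatment or assessments not yet completed, for a reason related to a compared outcome, and offers no option to stop only the test. That much follows from the text, with the baseline part conditional on assignment coming first.

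Whether the loss is informative, and in which direction, cannot be derived from the Protocol. The illustrative bias of 0.02 to 0.14 SD against active stimulation rests on assumed trigger rates, pain effect and correlations, and on complete loss of the strength value. It reverses in sign if stimulation makes the test more painful and vanishes if it does not affect pain. It is probably small beside sampling error. The firmer reason to change the rule is avoidable loss of randomised athletes and their data.

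**What to change.** Reword section 10.5 so that a pain increase stops that test and does not end participation. The athlete stays in the study in the assigned group, continues treatment if the responsible clinician judges it safe, and completes the remaining VAS, KOOS, IKDC and ACL-RSI. Add to the strength description in section 9 and in the section 10.7 procedure that trials recorded before a stop are kept, including the voluntary torque before a painful burst, and that strength is the mean of the completed trials. Report stops by arm and visit.

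The cost is one reworded sentence and a few words in two places. Some means will rest on fewer than five trials. With single-trial reliability R, the SD of a mean of m trials relative to five is √{[R + (1 − R)/m] / [R + (1 − R)/5]}. At an assumed R of 0.85, 0.90 and 0.95 this is 1.066, 1.043 and 1.021 for one trial, and 1.011, 1.007 and 1.003 for three: an increase of 2% to 7% with one trial and about 1% or less with three.

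The change does not rescue every strength value. An athlete stopped during the unrecorded practice contractions or in the first recorded trial may still have none, but would keep treatment where safe and the questionnaire outcomes.
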